### Intervention Fidelity

A core component of the intervention is the completion of a daily sleep diary, which supports both treatment delivery and progress monitoring. To assess adherence, participants will complete a brief questionnaire on diary compliance through their PROTECT Norge study dashboard. The PROTECT Norge infrastructure for real-time tracking of all study activities, including study activity status. Study help desk staff will manually monitor study activity in real time, including diary entries and assessment completion. These data will allow real-time monitoring of adherence. They will be asked to complete and submit this compliance log within a reasonable timeframe following the end of the intervention. For each day of the study, participants will indicate whether the diary was completed in the morning, evening, or both, with additional options for “I do not know” or “Did not complete.” This structured measure of adherence provides insight into participant engagement and supports evaluation of intervention fidelity.

### Outcome Assessment Timing

Baseline data will be obtained from all potential participants as part of the screening. At 3 months postrandomization, a similar data collection will be performed. These data will serve as the primary short-term outcome data for the study. For the waitlist group, they will also serve as an updated baseline for their intervention period, which starts immediately after they provided these data (see Textbox 1).

Textbox 1.Overview of data collection time points.
**Intervention arm**
T0: BaselineT0 to T1: InterventionT1 (T0+3 mo): Follow-up (FU) 1T2 (T0+6 mo): FU2T3 (T0+12 mo): FU3
**Control arm**
T0: BaselineT0 to T1: Waiting listT1 (T0+3 mo): FU1T2 (T0+6 mo): Not applicableT3 (T0+12 mo): Not applicableT0’=T1: Updated baselineT0’ to T1’: InterventionT1’ (T0’+3 mo): FU1’T2’ (T0’+6 mo): FU2’T3’ (T0’+12 mo): FU3’

### Outcomes

Study outcomes will be evaluated using validated instruments to capture the effects of the intervention on sleep, cognition, and related mental health domains through PROTECT Norge built-in clinical trials infrastructure. The primary outcome is insomnia severity, assessed using the ISI. All other outcomes are considered secondary outcomes (see Table 2 for details). Use of sleep medication is a secondary outcome and will be captured on a daily interval through the digital sleep diary.

**Table 2. T2:** Screening instruments and outcome measures used in the study, assessed through the Platform for Research Online to Investigate Cognition and Genetics in Ageing (PROTECT) Norge infrastructure.

Short name	Long name	Details	Time frame	Assessment points
ISI	Insomnia Severity Index [25]	7 items; scale 0-28, higher scores indicate more severe insomnia symptoms.	Past 2 wk	Screening/baseline + all follow-ups
SPD	Sleep problem duration item	One item assessing duration of sleep problem, scored 0=no sleep problem to 3=3 months or more	Current	Screening
GSAQ	Global Sleep Assessment Questionnaire [32]	Four separate items scored 0-4 will be used to screen for sleep disorders	Past 4 wk	Screening
FLAME	Factors of Longitudinal Attention, Memory and Executive Function [31]	Computerized neuropsychological battery with 8 tests. Gives composite score combining subscores on domains such as attention (speed and accuracy), memory, and executive function; higher scores reflect better overall cognitive performance.	Current	Baseline + all follow-ups
PHQ-9	Patient Health Questionnaire [33]	9 items; scale 0-27, higher scores indicate more severe depressive symptoms.	Past 2 wk	Baseline + all follow-ups
GAD-7	Generalized Anxiety Disorder scale [34]	7 items; scale 0-21, higher scores indicate more severe anxiety symptoms.	Past 2 wk	Baseline + all follow-ups

### Statistical Analysis

Descriptive statistics will be presented for baseline demographics, including age, gender, ethnicity, marital status, education, and employment status. Counts and percentages (categorical variables) and either means and SDs (symmetric continuous variables) or medians and IQR (skewed continuous variables) will be presented for the total sample and per intervention arm. Similarly, descriptive statistics will be presented for primary and secondary outcome variables, for all time points.

The primary estimand will be the average treatment effect (ATE), defined in accordance with the International Council for Harmonisation (ICH) E9(R1) guideline on estimands and sensitivity analysis as the adjusted mean difference in insomnia symptoms measured as ISI scores between the intervention and waitlist arms at three months postbaseline. Nonadherence will be handled using the treatment policy strategy (which reflects the intention-to-treat principle under the estimand framework), meaning that the analysis will include all participants according to their randomized allocation, regardless of adherence.

The primary inferential analysis will thus be the comparison of the intervention and the waitlist arms at 3 months post baseline with regard to mean ISI scores. This comparison will be performed using analysis of covariance (ANCOVA), implemented as a linear regression model with follow-up ISI as the dependent variable, intervention arm as the independent variable, and baseline ISI as a covariate. The interaction between intervention arm and baseline ISI will be included to allow for slope heterogeneity. To improve precision, further adjustments will be made for potentially predictive baseline variables, ie, the demographic variables listed above plus baseline measures of depression (Patient Health Questionnaire-9) and anxiety (Generalized Anxiety Disorder-7). All continuous covariates will be entered linearly. The primary contrast will be reported as a marginal (population average) mean difference, obtained via model-based standardization over the joint baseline covariate distribution of the randomized sample.

The estimated ATE will be reported with a 95% CI based on a heteroscedasticity-robust SE and corresponding 2-sided *P* value. An effect size will be calculated by dividing the ATE by the pooled SD of baseline ISI scores.

Missing 3-month ISI and any missing baseline covariates will be handled using multiple imputation by chained equations (MICE). Imputation models will include all variables specified for the substantive model plus auxiliary variables given by 3-month measures of Patient Health Questionnaire-9, Generalized Anxiety Disorder-7, and FLAME. A total of *m*=100 imputed datasets will be generated, using logistic regression for dichotomous variables and otherwise predictive mean matching (*k*=5). Each imputed dataset will be analyzed with the primary ANCOVA, and effect estimates and standard errors will be combined using Rubin rules.

Supplementary analyses will assess the complier average causal effect. Sensitivity to missing not at random dropouts will be explored in a tipping-point (delta) analysis, by applying additive shifts to the imputed three months ISI scores separately by arm. In case of substantial skewness of the outcome, explorative sensitivity analyses will apply either Box-Cox transformation of the outcome or other regression models.

For the assessment of long-term effects on insomnia symptoms, there is no control group; thus, no conclusions will be drawn regarding treatment effects. The longitudinal development of ISI scores from baseline to 3, 6, and 12 months will be studied in linear mixed models, including random intercepts and slopes to allow for correlation between repeated measurements. Data from the original intervention arm will be combined with the (3 mo + delayed) data from the original waitlist arm for these analyses. Time since baseline (updated baseline for the waitlist arm) will be treated as a categorical variable.

Secondary outcomes will be analyzed similarly to ISI scores, with assessment of treatment impact at three months and longitudinal descriptive analysis of long-term trajectories, including covariance with insomnia symptoms. However, all secondary analyses will be exploratory.

### Power Analysis

At present, more than 3500 active participants with an active consent for contact in the PROTECT cohort. With the planned expansion, approximately 5000 participants are expected to be available at study initiation. Assuming that 15% of these (approximately 750 individuals) will meet eligibility criteria, we aim to recruit 500 participants (approximately 67% of those eligible). Allowing for 20% attrition in both arms prior to the 3-month follow-up, we expect 400 participants to be available for the primary efficacy analysis (200 per arm). This sample size provides more than 80% power to detect a small-to-medium effect size of 0.3 using a 2-sided significance level of α=.05. Applying ANCOVA in the primary analysis is expected to further increase statistical power, depending on the proportion of variance explained (*R*^2^) by baseline variables.

### Ethical Considerations

This project will be conducted in accordance with the Declaration of Helsinki [35] and complies with the General Data Protection Regulation (GDPR, 2018) and Stavanger University Hospital’s data security policy.

The ASLEEP RCT will be conducted as a nested study within the PROTECT Norge infrastructure, which was launched in 2020 and approved by the Regional Committee for Medical and Health Research Ethics, West (REK vest, reference 2019/478). A separate application for ethical approval for the ASLEEP project will be submitted to REK, and internal approval will be sought at Stavanger University Hospital, including a data protection impact assessment for any new technology used to process participant data. Only participants who have previously provided broad consent (C4C) for future studies within PROTECT Norge will be invited, and all will provide additional written informed consent specific to the ASLEEP RCT study through a secure and validated procedure. Participation is voluntary, and participants may withdraw from the study at any time, without giving a reason. No financial compensation will be provided for participation.

All study data will be stored on secure cloud servers in Norway, with regular backups and monthly data transfers from the PROTECT Norge infrastructure to internal servers at Stavanger University Hospital. Any significant protocol modifications (eg, changes to eligibility criteria, outcomes, or analyses) will be submitted for review by the REK, updated in the trial registry and appropriate internal registries at Stavanger University Hospital. Personally identifiable information will be stored separately from research data, and data will be retained for 10 years following study completion and then permanently anonymized by deleting the reidentification key. Access to personally identifiable information will be restricted to authorized research personnel only.

Specifically for the phase 2 RCT, access to identifiable data will be restricted to authorized study staff with direct participant contact through the PROTECT Norge help desk via a secure, access-controlled management portal requiring authenticated login. Pseudonymized datasets will be used for data analysis by members of the research team involved in data analysis. Study staff responsible for system administration, participant support, and adherence monitoring may have access to operational study data but will not take part in data analysis.

Data quality will be ensured through standard platform-based validation procedures and institutional quality assurance routines.

A waitlist-controlled design has been chosen to ensure that all participants will ultimately receive access to the intervention while enabling robust evaluation. Given the low-risk nature of this behavioral, fully digital intervention, no physical harms are anticipated, but depression symptoms will be regularly monitored to identify any signs of distress or harmful behavior, with follow-up procedures in place to provide appropriate support if needed.

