Video module 3 (30 min 10 s)	Treatment of insomnia	This video module focuses on the management of insomnia, including definitions, prevalence, and treatment strategies for both short-term and chronic insomnia, as well as principles of sleep regulation. Additionally, [name] gives sleep hygiene advice, discussing ways to maintain sufficient sleep, support a healthy circadian rhythm, and minimize evening and nighttime arousal through habits and behavioral practices.

As part of phase 1 of the project, the ASLEEP advanced course will be developed and subsequently offered to participants in a fully digital RCT to assess its effect on sleep outcomes. Eligible participants who have completed the basic course will be funneled into the advanced course if their post–basic course score on the ISI [25] is 10 or higher (defined as symptoms of insomnia) [26].

The advanced course will be developed according to established protocol for CBT-I, drawing on core components such as sleep restriction, stimulus control, cognitive restructuring, sleep-hygiene reinforcement, and relapse prevention [27]. However, unlike other existing digital CBT-I programs (eg, SHUTi, Sleepio), which deliver these components within a single treatment stream, ASLEEP applies a stepped-care approach [28] in which only participants who continue to report insomnia symptoms after completing the basic course progress to the more treatment-intensive modules. The ASLEEP advanced course is expected to consist of a series of weekly digital modules delivered over approximately 6 weeks, although the exact number and pacing of modules will be finalized during the development phase. Consistent with evidence identifying sleep restriction and stimulus control as the most effective components of CBT-I [29], these components will constitute the core of the intervention. Sleep restriction aims to consolidate sleep and strengthen homeostatic sleep pressure by limiting time in bed to approximate actual sleep duration and gradually expanding it as sleep becomes more efficient [28]. Stimulus control complements this by re-establishing the bed and bedroom as cues for sleep rather than wakefulness through structured behavioral instructions, including going to bed only when sleepy, leaving the bed if unable to sleep, and maintaining consistent rise times.

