A sleep diary will be completed throughout the advanced course to track progress and to tailor individual intervention recommendations, including ongoing adjustment of the sleep-restriction schedule.

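### The harms statement expects no physical harm and names only depression for monitoring, although the core of the course restricts time in bed; as described, daytime sleepiness and physical unwanted effects are not recorded after randomisation

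*Protocol article*

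**What the plan says.** **Harms position.** The protocol article, Ethical Considerations, states: "Given the low-risk nature of this behavioral, fully digital intervention, no physical harms are anticipated, but depression symptoms will be regularly monitored". The stated aim of that monitoring is to pick up distress or harmful behaviour, with follow-up procedures for those who need support. No other effect is named for monitoring.

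**Core of the course.** The Intervention section makes sleep restriction and stimulus control the core of the advanced course. It explains that restriction is meant to consolidate sleep and to "strengthen homeostatic sleep pressure by limiting time in bed to approximate actual sleep duration", with time in bed extended as sleep efficiency improves. About 6 weekly modules are expected, but "the exact number and pacing of modules will be finalized during the development phase".

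**Measures after randomisation.** Table 2 (Outcomes) repeats the ISI, FLAME, PHQ-9 and GAD-7 at all follow-ups. The GSAQ is given at screening only: "Four separate items scored 0-4 will be used to screen for sleep disorders". Beyond Table 2 there are three further sources:
- The sleep diary: "A sleep diary will be completed throughout the advanced course to track progress" (Intervention). Sleep medication use "will be captured on a daily interval through the digital sleep diary" (Outcomes).
- The compliance log on diary completion (Intervention Fidelity).
- Help-desk tracking of study activity, whose stated use is adherence: "These data will allow real-time monitoring of adherence" (Intervention Fidelity).

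**Controlled period.** T1 is at 3 months. For the waitlist it doubles as the new baseline for its own intervention period, "which starts immediately after they provided these data" (Outcome Assessment Timing). Statistical Analysis confirms that there is no control group for long-term effects.

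**The concern.** The harms sentence rests on the intervention being behavioural and digital. That describes how the course is delivered, not what participants are asked to do. A component designed to build sleep pressure can be expected to make some people sleepier by day for a while, and the article's own account of the mechanism is enough to see this. The sentence therefore fits poorly with the Intervention section, and the one effect it names for monitoring is not the one that the mechanism points to.

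Two things are at stake. The first is participant safety during the restriction weeks: as described, nobody is asked whether they are unusually sleepy or have had an unwanted physical effect. The second is evidence. The article presents ASLEEP, if effective, as a scalable, low-threshold offer. A randomised comparison of tolerability would support that claim, and it is available only up to T1. Later follow-ups and the waitlist's own course can add uncontrolled data but cannot restore the comparison.

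**Working it through.** **1. The plan's own figure.** Power Analysis gives 500 recruited, 20% attrition, 200 per arm analysed, effect size 0.3, two-sided 5%, and power above 80%. Check: 500 × 0.8 = 400, or 200 per arm. The expected test statistic is 0.3 × √(200/2) = 3.0, so power ≈ Φ(3.0 − 1.96) = 85%. This reproduces and is not in dispute.

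**2. What each source after randomisation can show, as described.**

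| Source | Both arms up to T1? | What it can show |
|---|---|---|
| ISI | Yes | Worsening insomnia, past 2 weeks |
| PHQ-9, GAD-7 | Yes | Worsening mood or anxiety, past 2 weeks |
| FLAME | Yes | Cognition, including attention, on the day |
| Sleep diary | Described for the course; a waitlist diary is implied, not stated | Progress and medication use; other items not listed |
| Compliance log, help-desk tracking | Tied to the diary and study activity | Adherence |
| GSAQ | Screening only | Sleep disorders at entry |

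None is described as recording daytime sleepiness or physical unwanted effects.

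**3. Why recall at T1 should reach back to randomisation.** Assume 3 months = 13 weeks and a course that starts at randomisation. A 2-week look-back at T1 then runs from the end of week 11 to the end of week 13, which is 2/13 = 15% of the randomised period. Its overlap with a course of L weeks is max(0, L − 11):
- L = 6 (the article's expectation), and any length up to 11: 0 weeks.
- L = 12: 1 week (1/12 = 8% of the course).
- L = 13: 2 weeks (2/13 = 15%).

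A sleepiness item with the usual 2-week look-back would thus miss most or all of the restriction period. This informs the design of the fix; it does not measure a fault in the existing scales.

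**4. What an added T1 sleepiness item could deliver.** The article gives no event rates, so 10%, 20% and 30% are assumptions. The 95% CI half-width for the difference, with the same rate p in both arms, is 1.96 × √(2p(1 − p)/n). The last column is the increase over p detectable with 80% power at two-sided 5%.

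| n per arm | p | Half-width (points) | Detectable difference (points) |
|---|---|---|---|
| 200 | 10% | 5.9 | 10.0 |
| 200 | 20% | 7.8 | 12.3 |
| 200 | 30% | 9.0 | 13.5 |
| 160 | 10% | 6.6 | 11.4 |
| 160 | 20% | 8.8 | 13.8 |
| 160 | 30% | 10.0 | 15.1 |

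The rows with 160 apply if 400 are randomised, as the Abstract and Limitations say, with 20% attrition: 400 × 0.8 / 2 = 160.

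For rarer events a comparison says little: 3/200 against 0/200 gives Fisher p = 0.25. These should be listed by arm without a test.

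**The case against.** The strongest reply is that this is largely silence in a condensed article. Adverse-event recording is commonly left to the full protocol or the ethics application, and the latter has not yet been submitted. Diary items other than medication use are not listed, so a sleepiness item cannot be ruled out. The Introduction calls CBT-I safe. Time in bed is limited to roughly actual sleep duration and then extended, with continuing individual adjustment. Temporary sleepiness is arguably not a physical harm at all, and the article nowhere mentions falls or accidents.

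Much of this stands. It makes low risk a sound expectation and means that fuller reporting may already be intended. It does not remove the point, because the article does not merely stay silent: it states a harms position and names one effect to monitor, and that choice does not follow from the mechanism it describes. As a stage 1 registered report, it should state that position well.

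Two stronger readings are not supported:
- A reader might infer that no unwanted effect could be compared by arm. Deterioration in insomnia, mood, anxiety or cognition can be, because the ISI, PHQ-9, GAD-7 and FLAME are collected in both arms at T1.
- A reader might infer that the diary cannot serve as a two-arm source. Medication use is a diary-captured secondary outcome, and Statistical Analysis plans a 3-month treatment comparison for secondary outcomes. That implies a waitlist diary, although the article does not say so.

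**Conclusion.** The concern holds as a cheap improvement to safety monitoring. The stated harms position is narrower than the intervention's core component warrants. As described, daytime sleepiness and physical unwanted effects go unrecorded during the only period with a control group. The primary estimand, its analysis and the sample size are untouched, and no stated figure is wrong.

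The precision figures show what an added item could deliver: half-widths of about 6 to 10 points, and differences of about 10 to 15 points detectable. They rest on assumed rates and do not measure a defect. The recall figures rest on a 13-week period and a start at randomisation. That sleepiness is foreseeable is an inference from the described mechanism. The documents do not show that the course is unsafe or that adverse-event reporting will be absent from the full protocol.

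**What to change.** 1. **Reword the sentence in Ethical Considerations**, for example: *Serious physical harms are not expected, but sleep restriction may cause temporary daytime sleepiness, which will be recorded.*
2. **During the course**, add one item on sleepiness or unwanted effects to the diary or the weekly modules. Route positive answers to the follow-up procedures already mentioned. This item is for participant safety, not for comparing arms.
3. **At baseline and T1, in both arms**, add a brief daytime sleepiness item and an item on any unwanted effects, including falls or accidents. The T1 recall should cover the whole time since randomisation, so that it works whatever course length is chosen.
4. **Reporting:** summarise both items descriptively by arm, with a 95% CI for the difference in sleepiness only.

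**Cost.** A few items on an existing platform and a sentence in Outcomes, at a time when ethics approval has not been sought and the course is still being built. Questionnaires become slightly longer and the help desk will have some reports to route. The T1 answers will be unblinded self-report over about 13 weeks, so any difference between arms needs cautious reading.
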